## Abstract

**Background::**

The number of people living with the side effects of breast cancer treatment (eg, loss of muscular mass and muscular strength, upper-limb mobility and disability, lymphedema, cardiac toxicity, and reduced quality of life) is increasing yearly. These consequences can be improved through exercise, specially combining resistance and aerobic training. Previous exercise trials have not been consistent in applying training principles and standardized reporting, and this partly explains the variability in obtained results. The aim of this study is to assess the effect of a 12-week supervised resistance exercise program combined with home-based aerobic exercise, compared with home-based aerobic exercise only, on muscular strength and several aspects of health-related quality of life in breast cancer survivors. To maximize transparency, replicability, and clinical applicability, the intervention is described following the consensus on exercise reporting template.

**Methods::**

This study is a parallel-group randomized controlled trial in which 60 female breast cancer survivors, who have completed central treatments of the disease in the last 5 years, will be randomly assigned to either an experimental group that will perform a total of 24 progressive resistance training sessions for 12 weeks (ie, 2 weeks of individual training and 10 weeks of micro-group training) and will be requested to undertake 10,000 steps/d, or a control group that will be requested to undertake 10,000 steps/d, only. Outcomes will be evaluated at baseline and at week 12. Primary outcome measure is peak isometric muscular strength of the lower- and upper-body, assessed with several exercises through an electromechanical dynamometer. Secondary outcomes include cardiorespiratory fitness, upper-joint mobility and disability, health-related quality of life, cancer-related fatigue, depression, life satisfaction, and presence of lymphedema.

**Discussion::**

This study aims to investigate the extent to which a 12-week supervised and progressive resistance exercise program, in addition to home-based aerobic physical activity, might improve muscular strength and health-related quality of life in breast cancer survivors. The comprehensive description of the intervention will likely contribute to enhancing exercise prescription in this population.

**Trial registration number::**

ISRCTN14601208.

## Introduction

1

In women, breast cancer is the most commonly diagnosed type of cancer (ie, ∼2.1 million new cases every year) and the leading cause of death worldwide.^[1]^ The incidence of breast cancer in Spain is increasing. While there were approximately 26,000 new diagnoses in 2017, recent estimations anticipate over 32,000 diagnoses in 2019.^[2]^ In the city of Almería (ie, southern Spain) it is estimated that approximately 500 new cases appear yearly.^[3]^ Nevertheless, ongoing advances in early detection and treatment of breast cancer have led to a significant mortality reduction. For instance, survival following breast cancer, in a developed country such as Canada, has been reported to be of 87%.^[4]^ In Europe, breast cancer mortality is estimated to be reduced over 10% by 2020,^[5]^ with the exception of Spain, as Spain has the lowest mortality rate in Europe.^[5]^

The above-mentioned breast cancer mortality reduction over time implies that a yearly increasing population is living long after cancer diagnosis and treatment, thus facing many short-, mid-, and long-term side effects. Therefore, research addressing the management of the breast cancer-related side effects is of major clinical and public health relevance. Common side effects following breast cancer include the presence of lymphedema,^[6]^ cardiac toxicity,^[7]^ depression,^[8]^ fatigue,^[9]^ bone health issues, or obesity.^[10]^ These problems, together with a significant loss of upper limb mobility^[11,12]^ and a major loss of muscular strength and muscle mass, compromise life satisfaction and quality of life^[13]^ and are to be monitored in the follow-up of breast cancer.^[14]^ In particular, muscular strength during treatment has been reported to be 25% lower in lower extremities and 12% to 16% lower in upper extremities compared to healthy individuals,^[15]^ and similar trends seem to occur regarding cardiorespiratory fitness^[16,17]^ and upper limb function and mobility.^[11]^ It is important to note that this tendency might worsen in the absence of physical exercise following treatment.

Current guidelines for the management of breast cancer survivors include health promotion counseling related to physical activity.^[14]^ In this line, for ethical reasons, any exercise-based clinical trial should ensure that all trial participants, at least, meet the international physical activity guidelines (ie, at least 150 minutes per week^[18]^). In addition, structured physical exercise is an attractive option in the follow-up of breast cancer as it might counteract or, at least, benefit, several (if not all) of the above-mentioned side effects of breast cancer.^[19–22]^ In particular, resistance training has shown to enhance muscular function and body composition and, to some extent, fatigue, not only during treatment, but also in the long-term follow-up,^[23]^ and it is safe for limb-related issues such as lymphedema.^[24–27]^ Resistance training at least once a week has shown to reduce the mortality risk by 33% in breast cancer survivors.^[28]^

However, description of exercise interventions in exercise-based clinical trials, including breast cancer trials,^[29]^ has been consistently poor.^[30]^ In their recent systematic literature review, Neil-Sztramko et al^[29]^ concluded that “no studies of exercise in women with breast cancer attended to all principles of exercise training or reported all components of the exercise prescription in the methods, or adherence to the prescription in the results,” which precludes transparency and replicability of clinical trials in this population. The systematic review of Fairman et al^[31]^ revealed that resistance training prescription is very heterogeneous across studies and largely underdeveloped. Failure to apply the exercise principles may explain the heterogeneity observed across study outcomes in various systematic reviews and meta-analyses.^[20,32–36]^ This opens a window of opportunity for upcoming trials to correctly implement the exercise principles and provide comprehensive details of interventions,^[37]^ thus contributing to the development of future resistance training guidelines in breast cancer survivors.^[29]^

The primary aim of this study is to assess the effect of a 12-week supervised resistance exercise program combined with home-based aerobic training, compared with home-based aerobic training only, on muscular strength in breast cancer survivors. Secondary aims are to assess the effects of the intervention on cardiorespiratory fitness, upper-limb mobility and disability, health-related quality of life, cancer-related fatigue, depressive symptoms, life satisfaction, body composition, and lymphedema in this population.

## Material and methods

2

### Design and protocol registration

2.1

The EFICAN (Ejercicio FÍsico para pacientes con CÁNcer de mama) study is a parallel-group randomized controlled trial registered at the ISRCTN registry (ISRCTN14601208) on August 1, 2019, before the enrolment of participants begun (ie, on August 12, 2019).

### Setting and eligibility criteria

2.2

Participants have been recruited through local associations and advertisements in local newspapers, radio, and social media including social networks, and through referral from clinical oncologists from the Torrecárdenas University Hospital. Eligible participants are voluntary women aged 18 to 65 who have undergone breast cancer surgery and have finished core treatments (ie, chemotherapy and/or radiotherapy) in the past 5 years. The exclusion criteria are defined as follows:

(1)presenting with metastatic breast cancer,(2)awaiting breast reconstruction in the following 6 months,(3)presenting with any pathology that might prevent participants from exercising (ie, decompensated heart failure, unstable ischemic heart disease, severe untreated high blood pressure, moderate-severe valvopathies, aortic aneurysm, moderate-severe chronic obstructive pulmonary disease, pulmonary hypertension, chronic respiratory insufficiency), and(4)regularly performing >300 minutes per week of structured exercise. This study has been reviewed and approved by the Ethics Committee of the Torrecárdenas University Hospital, Almería, Spain (ref: Ejercicio-CáncerUAL[98/2019]), on July 31, 2019.

### Procedures

2.3

All potential voluntary participants fill out an online form indicating basic information about their disease, years from treatment termination, and so on. Potential participants who are eligible based on the form information attend a personal screening with our Medical Doctors (MD) at public health care centers. The MD conduct an initial screening and revise the clinical records to confirm that all inclusion criteria are met and that participants are able to undertake physical exercise, in case of being randomized to such group. The MD are also responsible for obtaining participant's informed consent. Subsequently, the participants who meet inclusion criteria attend the exercise laboratory at University of Almería to undertake the physical examination. This study follows the SPIRIT guidelines for randomized trials protocols.^[38]^ The funding source has no role in the study. All databases including personal information will be collected by the principal investigators ([name] and [name]) only, who will be responsible for protecting confidentiality.

### Sample size

2.4

The sample size was calculated for the primary outcome (ie, muscular strength) using Stata v.13 (StataCorp LP, College Station, TX). Based on the results of the meta-analysis by Strasser et al,^[23]^ a difference in the change between groups in lower limb muscle strength of at least 6.9 kg would be clinically relevant. Assuming a common standard deviation of 7.5 kg, a 90% power, an alpha error of 5%, and considering a potential dropout of 20%, we will aim at enrolling 60 participants.

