### Randomization, treatment allocation, and blinding

2.5

After baseline assessment, each participant will be randomized to either an experimental group (EG) or a waiting-list control group (CG). Before participant's recruitment, a blinded investigator ([name]) created a computer-generated simple randomization sequence, to allocate participants in either group. Individual allocations were held in sealed, opaque, and consecutively numbered envelopes. A member of the staff not involved in the trial assessment or interventions will open the envelopes in front of participants and assign them to the groups.

The data analysts and the primary outcome assessors will be blinded to the participant allocation. However, due to the nature of the intervention (ie, supervised resistance exercise), the participants will be aware of the group they are allocated to.

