
**Table 2 T2:**
[figure not shown]
Exercises that are to be performed along the resistance training program^∗^.

All participants will be instructed to report any difficulties, limitations or needs so that the intervention can be adapted to individual needs. To maximize adherence, participants will be sent motivational messages (ie, either through WhatsApp or email) every 2 weeks, and participants who miss sessions will be contacted to ask for reasons and reallocate the schedule to undertake the session another day. Adherence to the program will be reported as the median attendance frequency and the proportion of patients attending ≥75% (ie, 18 sessions; the minimum pre-defined attendance to assess efficacy). Adherence to the exercise program, potential adverse events, and other relevant information will be measured throughout the whole intervention period using a comprehensive tally sheet to be completed daily by the PT during and after each training session. The detailed tally sheet to be used in this study, based on a previous well-designed exercise protocol,^[51]^ is shown as additional file (Table S3). There will not be any nonexercise component in this intervention.

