### Statistical analysis

2.9

The distribution of the main study variables will be assessed through histogram and Q-Q plots. Descriptive characteristics will be presented using the mean and standard deviation for normally distributed quantitative variables, the median and interquartile range for non-normally distributed quantitative variables, and the number and frequency for categorical variables. The comparability of the groups will be checked at baseline and potential confounders that present baseline group differences will be included in the analyses. The between-group differences in the primary and secondary outcomes will be assessed through linear or quantile regression, as appropriate. As we aim at assessing efficacy, the primary analyses are defined as per-protocol, where participants from the exercise group will be included if their attendance to the exercise sessions is ≥75%. Sensitivity analyses will also be carried out using a minimum attendance of ≥90% and using the intention-to-treat principle. Blinded investigators ([name] and [name]) will handle all hypothesis testing. The main analyses will be conducted with Stata v.13.1 (StataCorp LP, College Station, TX). Statistical significance will be set at *P* < .05.

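### Sixty enrolled with 20% dropout leaves 48 evaluable women, too few for the stated 90% power on the protocol's own inputs (about 88% to 89%)

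*Protocol article*

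**What the plan says.** Section 2.4 (Sample size) takes its target from lower-limb strength: "a difference in the change between groups in lower limb muscle strength of at least 6.9 kg would be clinically relevant". The remaining inputs are a common SD of 7.5 kg, 90% power and 5% alpha, followed by the enrolment figure: "considering a potential dropout of 20%, we will aim at enrolling 60 participants". The section gives neither the evaluable number per arm nor the step from that number to 60.

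Section 2.5 describes the allocation: the investigator "created a computer-generated simple randomization sequence, to allocate participants in either group". No ratio is stated and no blocking is mentioned.

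Section 2.9 (Statistical analysis) fixes the primary analysis set: "the primary analyses are defined as per-protocol, where participants from the exercise group will be included if their attendance to the exercise sessions is ≥75" per cent. Intention-to-treat is kept as a sensitivity analysis. Section 2.6.1, in the text after Table 2, puts the attendance threshold at 18 of the 24 sessions and calls it "the minimum pre-defined attendance to assess efficacy".

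**The concern.** A reader of section 2.4 will conclude that the trial keeps 90% power after losing a fifth of its participants. To allow for a loss of d, the evaluable need is divided by (1 − d). With the stated inputs, 60 appears too low to result from that step.

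There is a second question. The calculation allows only for dropout, but the primary analysis also drops exercise-arm women for low attendance. A woman who attends 17 sessions and completes the week-12 assessment has not dropped out of the study, yet she is not in the primary analysis. If the 20% was not meant to include such women, the quoted power does not describe the analysis named as primary.

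**Working it through.** **Inputs**
- Difference 6.9 kg, SD 7.5 kg, power 90%, alpha 5%, dropout 20%: section 2.4.
- Two-sided test: assumed, because the protocol does not state sidedness.
- Equal arms: assumed, because no ratio is stated.

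**Evaluable need**
- Normal approximation: n per arm = 2 × (1.960 + 1.2816)² × (7.5/6.9)² = 24.83, so 25 per arm and 50 in total. Power at 25 per arm is 90.2%.
- Noncentral t: 25 per arm gives 89.0% and 26 per arm gives 90.2%, so 26 per arm and 52 in total.

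**Reproducing the stated 60**
- 50 × 1.2 = 60.
- Alternatively, 24.83 rounded down to 24, and 24/0.8 = 30 per arm, again 60.
- The t-test need gives 52 × 1.2 = 62.4 (63) or 52/0.8 = 65, not 60.
- A one-sided 5% test needs 21 per arm, 42 in total. That gives 42 × 1.2 = 50.4 (51) or 42/0.8 = 52.5 (53), not 60.

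**Inflation for 20% loss**
- Normal: 50/0.8 = 62.5, so 63, or 64 with equal arms (25/0.8 = 31.25, so 32 each).
- t test: 52/0.8 = 65, or 66 with equal arms (26/0.8 = 32.5, so 33 each).
- Rounding does not account for the gap: the unrounded total of 2 × 24.83 = 49.66 already exceeds 48.

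**What 60 delivers**
- 60 × 0.8 = 48, or 24 per arm.
- Normal: standard error = 7.5 × √(2/24) = 2.165; 6.9/2.165 − 1.960 = 1.227; power 89.0%.
- Noncentral t, 46 degrees of freedom: power 87.7%. Averaged over the arm sizes that simple randomization can produce with 48 evaluable: 87.0%.

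**Largest loss compatible with 90% power**
- Normal: 50 of 60 must be evaluable; 1 − 50/60 = 16.7%.
- t test: 52 of 60 must be evaluable; 1 − 52/60 = 13.3%.

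**If attendance exclusions come on top of the 20%** (the exclusion counts are assumed for illustration; the protocol gives none)

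| Exercise v control | Power, t test | Power, normal |
|---|---|---|
| 24 v 24 | 87.7% | 89.0% |
| 22 v 24 | 86.2% | 87.6% |
| 20 v 24 | 84.3% | 86.0% |
| 18 v 24 | 82.1% | 83.9% |

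If the 20% already includes low attenders, the first row applies and there is no further loss.

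**The case against.** The strongest reply is that the gap is trivial. The normal formula is the one that leads to 60, and on it 48 evaluable women give 89.0% against a stated 90%. The t test widens the gap to 2.3 points, but its own requirement does not lead to 60 by either route. That stands as a comment on size. It does not make the figure right, since 48 is below the need under both methods.

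Sidedness is also unstated, and under a one-sided 5% test 60 would be more than enough. However, 60 does not follow from a one-sided calculation, so that reading does not explain the number.

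A reader might infer that the need was certainly multiplied by 1.2 when it should have been divided by 0.8. The protocol does not show the step. Rounding down to 24 per arm and then dividing correctly gives the same 60, so the cause is open and only the shortfall is established.

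A reader might also infer that the per-protocol rule definitely costs further power. The documents do not support that. They do not define what the 20% covers, women who stop exercising and women who attend too little will overlap, and section 2.6.1 provides for contacting absentees and rescheduling missed sessions. The further loss is conditional on exclusion rates the protocol does not give.

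Finally, the primary outcomes are averaged z-scores of tests measured in newtons, so any power figure for a 6.9 kg difference is on the planning scale and not the analysed one. This is fair. It limits how precisely a corrected figure should be read, and applies equally to the stated 90%.

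**Conclusion.** The point holds, at modest size. Under the protocol's own inputs, with a two-sided test and equal arms assumed, 60 enrolled and 20% lost gives 89.0% power (normal) or 87.7% (t test), not 90%. Enrolment is 3 to 6 women below what the inputs require. The limit on tolerable loss depends on the method, about 17% (normal) or 13% (t test), and the planned 20% exceeds both.

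Whether power in the primary analysis set is lower again cannot be settled from the document; the figures of 82% to 86% (t test) illustrate the sensitivity and are not predictions. Nor is the shortfall in itself an argument for a different primary analysis set, which is a separate question. The discrepancy biases no estimate or test; it makes the stated power slightly too favourable.

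**What to change.** Correct section 2.4 without raising enrolment. Suggested wording:

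*Assuming a two-sided 5% test, 60 enrolled participants with 20% loss leave 48 evaluable (24 per arm), giving about 88% power by the t test (89% by the normal approximation) for a 6.9 kg difference. Power of 90% requires 52 evaluable (at most about 13% loss) by the t test, or 50 (about 17% loss) by the normal approximation. The 20% covers both dropout and exclusion from the per-protocol analysis for attendance below 75%.*

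The last sentence should stand only if that was the intention. If it was not, the section should state an expected exclusion rate and give the power for the resulting arm sizes. The sponsor should also show the evaluable number per arm and the inflation step, so that the total can be checked.

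The cost is a few sentences and a slightly less favourable stated power. No participant, procedure or analysis changes.

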### Randomization, treatment allocation, and blinding

2.5

After baseline assessment, each participant will be randomized to either an experimental group (EG) or a waiting-list control group (CG). Before participant's recruitment, a blinded investigator ([name]) created a computer-generated simple randomization sequence, to allocate participants in either group. Individual allocations were held in sealed, opaque, and consecutively numbered envelopes. A member of the staff not involved in the trial assessment or interventions will open the envelopes in front of participants and assign them to the groups.

The data analysts and the primary outcome assessors will be blinded to the participant allocation. However, due to the nature of the intervention (ie, supervised resistance exercise), the participants will be aware of the group they are allocated to.

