#### Experimental group

2.6.1

To maximize transparency and replicability of the exercise protocol, we followed the guidelines stated on the Consensus on Exercise Reporting Template (CERT; Table S1).^[37]^ Participants assigned to the intervention group will carry out 2 strength training sessions weekly for 12 weeks. These 12 weeks are divided into 2 phases: a first phase of individual training (ie, 1:1 ratio) with a duration of 2 weeks and a second phase of 10 weeks in which group (ie, 4–6 participants) workouts are performed. Therefore, the program comprises a total of 24 training sessions (ie, of 60 minutes duration). In addition, the participants will be requested to undertake home-based aerobic training consisting in meeting the physical activity guidelines of 10,000 steps per day.^[39,40]^ The compliance with this requirement will be monitored through the Z11 Smart Band (Smart&Sport, Shenzhen, China) activity bracelet. The supervised training sessions will be led by exercise professionals (i.e. personal trainers; PT) with a degree in Physical Activity and Sport Sciences and with specific training in exercise for breast cancer patients. The exercise program will be carried out in a fitness room at the Almeria town hall (400 m^2^), which is equipped with aerobic and resistance training areas. The detailed description of the exercise equipment to be used during the training program is presented as additional file (Table S2).

Table 1 summarizes the periodization of the resistance training program. During phase 1 (ie, weeks 1 and 2; individual sessions), each participant will perform a total of 4 sessions in which the exercise professional will determine individual needs and limitations (eg, shoulder mobility, pain, etc) and participants will learn basic movement patterns that will be required in the following phase. During phase 2 (ie, weeks 3–12; group sessions), the participants will undertake circuit training including mobility and stability exercises and resistance training. There will be several stations in which participants will perform an exercise before moving to the next station. The starting level of each participant will be set considering their baseline muscular strength and the work undertaken in weeks 1 and 2.

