### Outcome measures

2.7

All outcome measures will be assessed at baseline and at week 12 (ie, after concluding the intervention period). Baseline assessment will be carried out during the 14 days before the beginning of the intervention and follow-up assessments will be conducted in the following 10 days from finalizing the intervention. The principal investigators ([name] and [name]) are responsible for the dataset and will only distribute it between trial investigators who are included in the funded project.

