### Data collection procedure

2.8

Baseline (ie, from September 9 to September 20, 2019) and follow-up (from December 16 to December 20, 2019) evaluations will be performed at the Exercise Laboratory of the University of Almería. Each participant begins filling out online questionnaires including health-related quality of life, cancer-related fatigue, depression, life satisfaction, and a general sociodemographic questionnaire. Thereafter, body composition is assessed in a private room, followed by shoulder joint mobility and presence of lymphedema, upper- and lower-body muscular strength and cardiorespiratory fitness.

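### Simple randomisation of 60 women leaves arm sizes and baseline strength to chance, although strength is known before allocation; a baseline strength difference above 0.25 SD has about a one-in-three chance and could be made less likely

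*Protocol article*

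**What the plan says.** Section 2.5 (Randomization, treatment allocation, and blinding) states that before recruitment a blinded investigator "created a computer-generated simple randomization sequence, to allocate participants in either group". Allocations sit in sealed, opaque, numbered envelopes, opened by a staff member who takes no part in assessment or intervention. No block, stratum or minimisation factor is mentioned, and no allocation ratio is given.

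The same section places randomisation after baseline assessment. Section 2.7 says "All outcome measures will be assessed at baseline and at week 12", and section 2.8 includes upper- and lower-body strength in the baseline visit of 9 to 20 September 2019. Each woman's baseline strength is therefore known when she is allocated.

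Section 2.4 sets the size: "we will aim at enrolling 60 participants". The only protection stated against chance imbalance is in section 2.9, where group comparability is checked at baseline and "potential confounders that present baseline group differences will be included in the analyses". Baseline strength is not named as a fixed covariate.

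**The concern.** An unrestricted sequence does nothing to hold the arms near 30:30 or to balance the variable most likely to predict the primary outcome. In a trial of 60, moderate chance differences are common enough to plan for.

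Two things are at stake. Unequal arms lose a little precision. More importantly, if the arms start at visibly different strength, readers will doubt a small trial whose primary outcome is strength. The remedy in section 2.9 then depends on what the baseline table happens to show: whether baseline strength enters the model is settled after the data are seen. Both the allocation method and the analysis rule leave this one variable to chance.

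**Working it through.** **Inputs.** From section 2.4: 60 women, difference 6.9 kg, SD 7.5 kg, power 90%, alpha 5%, dropout 20%. Assumed because not stated: 1:1 allocation and a two-sided test.

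**The plan's own figure.** n per arm = 2 × (1.960 + 1.282)² × (7.5/6.9)² = 24.8, so 25 per arm and 50 in total. 50 × 1.2 = 60, as stated. (Dividing by 0.8 would give 63; that is a separate matter.)

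**Arm sizes.** The size of one arm is Binomial(60, 0.5).

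| Split or worse | Probability |
|---|---|
| 33:27 | 52% |
| 34:26 | 37% |
| 36:24 | 15.5% |
| 38:22 | 5.2% |

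The mean absolute difference is 6.15 women.

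**Cost in power** (noncentral t, protocol inputs).
- 60 analysed: 93.9% at 30:30 and 93.0% at 36:24. The average under simple randomisation is 93.5%.
- 48 analysed (20% lost): 87.7% at 24:24, 87.2% at 27:21 and 86.2% at 29:19. The average is 87.0%.

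The average loss from unequal arms is 0.4 point (93.9 − 93.5) or 0.7 point (87.7 − 87.0).

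**Baseline strength.** At 30:30 the standardised mean difference has standard error √(4/60) = 0.258.
- P(above 0.25 SD) = 2 × [1 − Φ(0.25/0.258)] = 33%.
- P(above 0.5 SD) = 2 × [1 − Φ(0.5/0.258)] = 5%.

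Averaging over the random arm sizes gives 34% and 5.5%. With 48 analysed the figures are 39% and 8%.

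**What an imbalance does to an unadjusted estimate.** Let r be the correlation between baseline and week-12 strength (not in the documents) and assume equal SDs. An imbalance of 0.25 SD shifts an unadjusted comparison of week-12 values by 0.25r, and one of changes by 0.25(1 − r) in the other direction. For r = 0.5, 0.7 and 0.9 this is 0.13, 0.18 and 0.23 SD for week-12 values, and 0.13, 0.08 and 0.03 SD for changes.

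**With stratified blocks.** A median split of a normal variable explains 2/π = 0.637 of its variance and leaves 0.363. The standard error of the baseline difference becomes √(0.363 × 4/60) = 0.156. P(above 0.25 SD) falls to about 11% and P(above 0.5 SD) to about 0.1%. A simulation with blocks of 4 gave 12% against 34% for the 0.25 SD threshold.

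**Stratification against baseline adjustment.** The standard error of an unadjusted week-12 comparison falls by 1 − √(1 − 0.637r²) with stratification. Under simple randomisation with baseline strength in the model it falls by about 1 − √(1 − r²).

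| r | Stratified, unadjusted | Baseline-adjusted |
|---|---|---|
| 0.5 | 8% | 13% |
| 0.7 | 17% | 29% |
| 0.9 | 30% | 56% |

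Prespecified adjustment therefore supplies most of the precision.

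**The case against.** Simple randomisation is valid, unbiased and the least predictable scheme there is. That has value here, since envelopes are opened in front of participants who then know their group. The power loss is trivial. Chance imbalance in strength can be handled by naming baseline strength as a covariate, without touching allocation. The per-protocol primary analysis removes only exercise-arm women who attend too little, so even 30:30 at allocation does not secure equal arms at analysis. All of this stands. It limits the point to a modest improvement and shifts the weight from arm sizes to baseline strength. It does not remove the point, because section 2.9 does not commit to baseline adjustment.

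Three stronger readings are tempting, and the documents do not support them.
- A reader might infer that large imbalance is likely. The figures say otherwise: 38:22 or worse, or a strength difference above 0.5 SD, each has about a 5% chance.
- A reader might infer bias. Allocation is random and the envelopes are concealed, so there is none from this source.
- A reader might infer that a large exercise arm would overload delivery, given "a first phase of individual training (ie, 1:1 ratio) with a duration of 2 weeks". At two 60-minute sessions a week, 36 exercisers need 72 one-to-one hours weekly rather than 60. But 36 or more exercisers has only a 7.8% chance (half of 15.5%), and the article states no trainer number or capacity limit. Six groups of 4 to 6 hold any arm from 24 to 36, which covers 91% of outcomes.

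The objection also bears on the remedy. Blocks of 2 would give away too much. The primary strength measures are z-score composites, on which a cut-off fixed in advance is awkward. Stratifying on one lower-body test does not directly balance upper-body strength.

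**Conclusion.** The point holds as a low-severity matter of precision and credibility. Under an assumed 1:1 ratio, simple randomisation of 60 women gives a 37% chance of 34:26 or worse, about a one-in-three chance of a baseline strength difference above 0.25 SD, and about a 5% chance of one above 0.5 SD. The arm-size part is minor. The strength part deserves attention because the measurement is in hand before allocation and the stated adjustment rule is data-driven. Stratified blocks would cut the one-in-three chance to roughly 11–12%, assuming a normal distribution and a cut-off near the median. The further precision figures rest on an assumed baseline-to-outcome correlation.

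**What to change.** 1. For women not yet allocated, replace the sequence with computer-generated permuted blocks of randomly varying size, for example 4 and 6 but not 2. Keep block sizes from recruiting and assessing staff, and keep the sealed, opaque, numbered envelopes and the uninvolved opener.
2. If feasible, stratify on one raw baseline strength test in N, not a z-score, at a cut-off set before allocation and as near the expected median as can be judged. A badly placed cut-off leaves one stratum small and gains little.
3. In section 2.9, prespecify baseline strength (and the stratum, if used) as covariates in the primary model whatever the observed balance. This step is worth taking even if allocation is left as it is.

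The cost is a new list, a second envelope series if stratified, and a documented amendment, because the sequence was made before recruitment and enrolment began on 12 August 2019. Allocation becomes slightly more predictable near block ends. If some women are already allocated, the trial will contain two schemes, which should be reported. Stratifying on a lower-body test leaves upper-body balance largely to chance, so step 3 is needed there too.
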